## Abstract

**Background:**

Mixed partial thickness burns are the most common depth of burn injury managed at a large Australian paediatric hospital specialty burns unit. Prolonged time until re-epithelialisation is associated with increased burn depth and scar formation. Whilst current wound management approaches have benefits such as anti-microbial cover, these are not without inherent limitations including multiple dressing changes. The Biobrane® RECELL® Autologous skin Cell suspension and Silver dressings (BRACS) trial aims to identify the most effective wound management approach for mixed partial thickness injuries in children.

**Methods:**

All children presenting with an acute burn injury to the study site will be screened for eligibility. This is a single-centre, three-arm, parallel group, randomised trial. Children younger than 16 years, with burns ≥ 5% total body surface area involving any anatomical location, up to 48 h after the burn injury, and of a superficial partial to mid-dermal depth, will be included. A sample size of 84 participants will be randomised to standard silver dressing or a Regenerative Epithelial Suspension (RES™) with Biobrane® or Biobrane® alone. The first dressing will be applied under general anaesthesia and subsequent dressings will be changed every 3 to 5 days until the wound is ≥ 95% re-epithelialised, with re-epithelialisation time the primary outcome. Secondary outcomes of acute pain, acute itch, scar severity, health-related quality of life, treatment satisfaction, dressing application ease and healthcare resource use will be assessed at each dressing change and 3, 6 and 12 months post-burn injury.

**Discussion:**

The findings of this study can potentially change the wound management approach for superficial partial to mid-dermal burns in children locally and worldwide.

**Trial registration:**

The Australian New Zealand Clinical Trials Registry (ACTRN12618000245291) approved prospective registration on 15 February 2018. Registration details can be viewed at https://www.anzctr.org.au/Trial/Registration/TrialReview.aspx?id=374272&isReview=true.

## Background

Burns are the fifth most common cause of non-fatal injuries in children younger than 16 years [1]. Paediatric burn injuries are associated with the burden of both functional and psychological challenges to the child [2–4] as well as the considerable expense incurred to health service providers who manage the burn care [5]. In 2017, three-fourths of acute burns treated at the Queensland Children’s Hospital in Brisbane and approximately half of recorded burn cases across Australia and New Zealand [6] were partial thickness burn injuries. The available wound management options are not without inherent disadvantages including but not limited to delayed wound healing [7–12]. Thus, current practice is driven to facilitate faster wound re-epithelialisation to improve scar outcomes [13] and reduce healthcare costs [10, 14].

Partial thickness burn injuries have a varied time to re-epithelialisation. Superficial partial thickness burns ideally heal within 14 days without requiring surgical intervention. Typically, deep partial thickness wounds are anticipated to have a prolonged time to re-epithelialisation (TTRE), often requiring a skin graft. Mid-dermal thickness wounds can potentially re-epithelialise spontaneously, within 14 days and without surgical intervention [15]. However, this is not always the status quo and management of intermediate depth burns remains contentious. Some surgeons prefer early skin grafting, whereas others advocate for conservative non-surgical management.

One third of paediatric burns will develop hypertrophic scar, if wound re-epithelialisation occurs between 14 and 21 days [15–17]. It is presumed that children have an increased collagen production rate hence the higher incidence of hypertrophic scar formation as compared with adults [18]. In a systematic review, Vloemans et al. found that membranous dressings were better than topical standard of care options for the treatment of partial thickness scald burns in children [19]. However, there was no clear recommendation regarding the best membranous dressing for treatment of partial thickness paediatric burns [16]. Burn depth, TTRE and hypertrophic scar have an established association [13, 15–17]. Yet, despite advances in wound management approaches, the ideal dressing to manage partial thickness burns in children remains undefined. The three wound management approaches to be investigated in this trial are a topical anti-microbial dressing, epidermal replacement using an autologous skin cell suspension and dermal salvage using a biosynthetic skin substitute.

Topical silver impregnated dressings used as the standard of care at the study site are (i) Acticoat® (Smith and Nephew, Hull, UK) with Mepitel® (Mölnlycke, Göteborg, Sweden) or (ii) Mepilex Ag® (Mölnlycke, Göteborg, Sweden) alone [9]. Acticoat®, is a multi-layered polyethylene nanocrystalline silver pad that is attached to a soaking coat of polyester [20] and has been in clinical use since 1993. When compared to silver sulphadiazine ointment, Acticoat® is safe, cost-effective and reduces the TTRE, requirement for grafting and long term scar management in paediatric burn injuries [21–23] . Mepitel® is a silicone-coated, nylon dressing with a silicone wound interface layer. Acticoat® combined with Mepitel deliver antimicrobial properties of silver nanocrystalline particles and an atraumatic pain-free wound contact layer. This promotes faster re-epithelialisation by minimising wound-related trauma and pain [24].

Mepilex Ag® is a silver sulfate soft silicone foam dressing that allows for continuous silver delivery to the wound, good exudate management, provides a moist environment and thermal insulation making this dressing ideal for partial thickness burns [25]. In a randomised trial of children (*n* = 96) with partial thickness burns, silver-impregnated foam dressings were effective in shortening the TTRE and reduced pain during dressing changes [9]. Despite this, silver impregnated dressings are more expensive per dressing change when compared to Biobrane® and a Regenerative Epithelial Suspension (RES™) [10], require frequent dressing changes due to non-transparent design and are associate with adverse effects such as cytotoxicity and argyria. Over the last 30 years, epithelial suspension preparation for burn wound management has undergone a multitude of transformations including the number of enzymatic degradation agents used, co-delivery systems with various cell carriers and a range of preparation times (few weeks to under an hour) [7, 26]. The RECELL® Autologous Cell Harvesting (ACH) device (Avita Medical, California, USA) was first introduced almost two decades ago [27]. In approximately 30 min, a Regenerative Epithelial Suspension (RES™) containing basal keratinocytes, melanocytes, fibroblasts, melanocytes, Langerhans cells and epidermal basal cells [28] is obtained from a donor skin sample as small as 1 cm^2^. The faster preparation allows for a readily available suspension compared to the cultured keratinocytes, where wait times can be a few weeks.

Few studies have comprehensively assessed the effectiveness of the RES™ in the management of childhood burn injuries. Most of the published literature is based on the adult cohort and there is a paucity of data based on the paediatric population. When compared to standard care, wounds treated with RES™ had longer operative times [29], more wound infection [10] and once applied the RES™ requires a retention dressing such as Biobrane®, to keep *in situ* [10]. However, in the other studies, application of RES™ was associated with less post-operative pain [10, 29], smaller donor site area [29, 30], shorter TTRE [10, 29, 30], fewer dressing changes and cost-effectiveness [10, 31]. Autologous skin cell suspensions show promising potential to change current burn wound management approaches from dressing based to cell-based therapy.

First introduced in 1979 [11], Biobrane® (Smith and Nephew, Hull, UK) is a composite biosynthetic skin substitute composed a matrix of short porcine collagen peptides bonded to a layer of nylon that is enveloped in silicone [8]. The benefits of using Biobrane® include shorter TTRE, improved mobility, shorter hospital stay, ease of application, ability to visualise the wound [32] and reduced pain [10–12, 33, 34]. For clean wounds, this transparent dressing is able to stay *in situ* for up to 14 days, thus supporting the cost-effective treatment of burn injuries [35]. Failure of Biobrane® to adhere to the wound bed occurs once counts exceed 10^5^ organisms/gram of tissue [36]. Reported infection rates associated with Biobrane® range from 5 to 22% [12, 37, 38]. However, Lal. et al. demonstrated that infection rate upon application of Biobrane® to superficial partial thickness scald burns in children with 48 h of injury did not differ when compared to a topical silver dressing [39]. Biobrane® recreates the barrier function of the skin and has been used as a dermal salvage option for burn wounds over the last four decades.

### Aims

The Biobrane®, RECELL® Autologous skin Cell suspension and Silver dressings Trial (BRACS Trial), will evaluate partial thickness, paediatric and burn injuries with the following aims:

#### Primary

To evaluate the effectiveness of three wound management approaches (standard care silver dressings (Acticoat® and Mepitel® or Mepilex Ag®)) or an autologous skin cell suspension (ASCS, harvested with the RECELL® ACH device) with Biobrane® or Biobrane® alone, in reducing the re-epithelialisation time of superficial partial to mid-dermal thickness burn injuries in children.

#### Secondary

To examine the effectiveness of three wound management approaches in the same group of children for reducing pain, itch, scar severity and healthcare resource use as well as, improving health-related quality of life, treatment satisfaction and dressing application ease.

### Study design

The BRACS Trial is a parallel group, single-centre and randomised trial. The null hypothesis is that there is no difference between the three intervention groups. The alternative hypothesis is that there is a statistically significant difference between the interventions. If null hypothesis is not rejected, this is still important, as treating clinicians will be able to select an intervention knowing that patient well-being will not be compromised. An active treatment control group (group A: standard silver dressings) was included as it was considered unethical to use a placebo group for this study.

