## Data management

### Sample size estimate

The sample size estimate conducted for this trial is based on the primary outcome of TTRE. Using the Power Analysis and Sample Size (PASS) software (version 11.0.7; PASS, NCSS, LLC), a two-sided logrank test procedure was used. A total sample size of 84 subjects (28 participants per group) that accounted for a 10% attrition rate would achieve 80% power at a significance level of 0.05 [10, 75, 76]. A clinically important difference of 4 days for re-epithelialisation was used for the sample size estimation.

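### A non-significant result cannot show that well-being is not compromised: the trial is sized only to detect a difference in healing time and sets no equivalence or non-inferiority margin

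*Protocol article*

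**What the plan says.** The protocol article, Study design, sets up a conventional difference test: "The null hypothesis is that there is no difference between the three intervention groups", and "The alternative hypothesis is that there is a statistically significant difference between the interventions". It then gives a reason why non-rejection would still be useful, namely that "treating clinicians will be able to select an intervention knowing that patient well-being will not be compromised".

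Under Sample size estimate, "a two-sided logrank test procedure was used". The result is given as "A total sample size of 84 subjects (28 participants per group) that accounted for a 10% attrition rate", which "would achieve 80% power at a significance level of 0.05". The effect is stated in days: "A clinically important difference of 4 days for re-epithelialisation was used for the sample size estimation".

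Statistical analysis plans Kaplan-Meier and Cox regression for TTRE, with significance at p < 0.05. Neither section, nor the Discussion, gives an equivalence or non-inferiority hypothesis, a margin, or a rule that compares a confidence interval with a margin.

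**The concern.** Failing to reject a null of no difference means that the data are compatible with no difference. They may equally be compatible with a difference that matters. The Study design text goes further and says clinicians would then know that no child is worse off, whichever dressing is chosen. That is a conclusion of equivalence or non-inferiority, and the design has no means of reaching it.

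The conclusion is also wider than the outcome on which the trial is sized. Well-being is not defined, but it would naturally include pain, itch, scarring and quality of life. These are secondary outcomes with no stated power.

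At stake is the interpretation of a null result. The abstract says the findings could change practice locally and worldwide. An imprecise result, read as the protocol proposes, would be taken as support for free choice between the dressings.

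**Working it through.** **Inputs from the protocol (Sample size estimate).** Two-sided alpha 0.05; power 80%; 28 per group; 10% attrition; important difference 4 days. No hazard ratio, control median or SD of TTRE is given.

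**The plan's own figure.** 25 / 0.90 = 27.8, rounded up to 28 per group and 84 in total. The attrition step therefore fits 25 evaluable children per group. The 25 itself cannot be reproduced without a hazard ratio, median or SD. This does not show that 84 is wrong.

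**Miss rate at the design effect.** 1 − 0.80 = 0.20. One trial in five would fail to reject when the planned difference is real.

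**Precision on the hazard-ratio scale.** Assume all 25 per arm reach the endpoint, which is healing or skin graft (Primary outcome: TTRE).
- Half-width of the 95% interval for log HR: 1.96 × √(1/25 + 1/25) = 0.554.
- Observed HR 1.0: exp(±0.554) gives 0.57 to 1.74.
- Just non-significant result, observed HR about 0.57: lower limit exp(−2 × 0.554) = 0.33.

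**Chance of a non-significant pairwise test with 50 events**, by assumed true healing HR:

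| True HR | P(non-significant) |
|---|---|
| 0.50 | 31% |
| 0.60 | 56% |
| 0.70 | 76% |
| 0.75 | 83% |

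**Precision in days.** The SD must be assumed. The value that gives 80% power for 4 days with 25 per arm on a means scale is 4 / [(1.96 + 0.842) × √(2/25)] = 5.05 days.
- Half-width: 1.96 × 5.05 × √(2/25) = 2.8 days.
- A just non-significant estimate is about 2.8 days, so its upper limit is about 2 × 2.8 = 5.6 days.
- Range over other SDs, as twice the half-width: SD 4, 2 × 2.22 = 4.4 days; SD 6, 2 × 3.33 = 6.7 days; SD 7, 2 × 3.88 = 7.8 days. All exceed 4 days. Only an SD near 5 agrees with the stated 80% power; at SD 7, power would be about 52%.

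**What a non-inferiority claim would need.** These figures are illustrative, since no margin is stated. With no true difference, one-sided alpha 0.025 and 80% power, events per pair = 4 × (1.96 + 0.842)² / (ln margin)². A healing-HR margin of 0.67 needs 196 events, or 196 / 2 / 0.9 ≈ 109 per arm. A margin of 0.80 needs 631 events, about 351 per arm. The planned 50 events would give about 29% and 12% power respectively.

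**The case against.** The strongest reply is that the sentence is a rationale, not an analysis rule. No test, estimate or sample size depends on it, and the planned Kaplan-Meier and Cox analyses would be the same without it. That stands, and it limits the severity. It does not make the stated conclusion valid.

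A reader might also infer more than the documents support:

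- **That a null result is likely.** This depends on the true effect, which the protocol does not give. The only probability that follows from its own figures is 20% at the design difference.
- **That well-being would be judged on TTRE alone.** The stated null names no outcome. The trial collects pain, itch, scar severity and quality of life and monitors adverse events. The fair criticism is that it is not sized for these, not that it ignores them.
- **That the infection rates in the Background show the sentence to be unsafe.** The Background gives 5 to 22% for Biobrane, but also cites a comparison in children with scalds that found no difference from a topical silver dressing. The evidence is mixed and does not carry the point.
- **That any null result would be uninformative in days.** An estimate of exactly zero would have an interval of about ±2.8 days at SD 5 and ±3.9 at SD 7, and both exclude 4 days. At SD 5, 25 per arm would even give 80% power for non-inferiority with a 4-day margin. But no such margin is set, and that conclusion would come from comparing the interval with the margin, not from p above 0.05. The problem lies with non-significant estimates away from zero, which the protocol's sentence would treat in the same way.

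**Conclusion.** The point holds and should be fixed. The protocol states a conclusion from non-rejection that a superiority test without a margin cannot give. The logical fault depends on no assumption; the numbers show only its size. A real difference of the planned size is missed 20% of the time. An observed hazard ratio of 1.0 would still be compatible with about 0.57 to 1.74, assuming 25 events per arm. A just non-significant result would leave about 5.6 days' delay unexcluded, assuming an SD of about 5 days.

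The SD and the event count are back-solved or assumed, and the hazard-ratio and day scales need not correspond. The large dropout that the Discussion anticipates could widen the intervals. The documents do not support reading this as an error in the planned analysis or in the sample size of 84.

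**What to change.** Delete the sentence on non-rejection in Study design and replace it with text such as:

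> A non-significant result will be regarded as inconclusive. Pairwise effect estimates for TTRE will be reported with 95% confidence intervals. Failure to reject the null hypothesis will not be used to claim that the dressings are equivalent or that well-being is not compromised.

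Do not add a criterion that calls arms similar when the interval lies within 4 days. The 4 days is the difference the trial is sized to detect, not a justified margin, and Cox regression does not yield a difference in days. Such a criterion would also perform poorly. It would require an observed difference below 4 − 2.77 = 1.23 days at SD 5, or 4 − 3.88 = 0.12 days at SD 7. Truly identical arms would meet it only about 62% and 5% of the time. If a claim of similarity is wanted, it needs its own justified margin and a sample size to match.

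The cost is wording only: no change to the analysis, the data or the number of children. The permitted conclusion becomes less favourable. The change is most credible if made before comparative results are seen.

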## Methods

### Study setting

This single-centre study will be conducted at a major paediatric burn centre in Brisbane, Queensland, Australia. This large state hospital has a catchment area spanning more than 1.73 million km^2^ and with a population of approximately 5 million inhabitants [40]. The centre treats over 1200 new burns patients annually.

### Eligibility criteria

All new patients attending the study site will be evaluated for eligibility. Children younger than 16 years, who have sustained a burn of superficial partial thickness to mid-dermal depth, within 48 h of injury and with a total body surface area burned (TBSAB) ≥ 5% as assessed by the attending burns surgeon, will be included. To allow for patients who travel from regional referring centres to be included, application of silver-impregnated dressings onto wounds prior transfer to the study setting will be included. Patients with superficial burns, deep dermal to full thickness depth wounds and injuries deemed not compatible with life by the attending burns surgeon, will be excluded from participation in the study, see Fig. 1.

**Fig. 1 Fig1:**
[figure not shown]
Biobrane^®^, RECELL® Autologous skin Cell suspension and Silver dressings (BRACS) Trial flow diagram. *SPT* superficial partial thickness, *MD* mid-dermal, TBSAB total body surface area burned, *RES™* Regenerative Epithelial Suspension, *HRU* Healthcare Resource Use, *HRQOL* Health-related quality of life, *OPD* outpatient department

### Recruitment

Treating clinicians of all children presenting to the study setting will determine eligibility for enrolment in the study based on the set inclusion and exclusion criteria. Participant (where applicable) ‘assent’ is sought at the recruitment of each potential participant. Once guardian permission is confirmed, informed consent for participation will be obtained by an investigator aligned with the study. A translator will be present for all participants of non-English speaking background throughout the study. All participants and their guardians will be given an opportunity to discuss the study with the investigator prior to signed consent. Participants, who decline enrolment into the study, will be assigned standard care and only their de-identified data will be collected.

### Interventions

Eligible participants will be randomised to one of the three interventions:
Group A: standard silver dressings. Silver dressings will be applied ((i) Acticoat® with Mepitel® or (ii) Mepilex Ag®) as per standard protocol at the study site.Group B: Biobrane® combined with RES™Group C: Biobrane® only.

### Operative procedures

The initial dressing application will be completed under a general anaesthesia for all consented participants under aseptic conditions. The operative timeline is illustrated in Table 1. For eligibility to enrol, the attending burns surgeon will determine TBSAB and this will be the primary approach for TBSAB assessment. The inaccuracy of human TBSAB assessment arises from variability associated with children, body mass index and gender [41]. Consequently, the secondary measure to estimate TBSAB will be the NSW Trauma Application and E-Burn Application. Available software programs have found some application but not much validation [42–44] and stems from the idea of rapid accurate TBSAB calculation to guide subsequent management. These mobile applications facilitate instant TBSAB calculation and both are used at the study centre and worldwide.

**Table 1 Tab1:**
[figure not shown]
Initial dressing application procedure

*RES*^*TM*^ Regenerative Epidermal Suspension, *ACH* Autologous cell farvesting, *FR* French gauge

Objective burn depth will be measured with the Moor LDLS-BI Laser Doppler Imager® (Moor Instruments Ltd., Axminster, and Devon, UK). The reported sensitivity and specificity of Laser Doppler Imaging (LDI) in predicting outcome of paediatric injuries when compared with clinician assessment ranges from 80.6–97% and 76.9–100% [45–47], respectively. The assessment of burn depth by the attending burns surgeon will be taken as the primary approach. Burn depth assessed with LDI will be the secondary approach and measured at the initial dressing application after randomisation. Burn depth assessment using LDI in the first 48 h post-burn injury has been showed to be accurate [48–51] and is used to record burn depth progression and not guide clinical practice at the study site.

A three-part process will be required for the initial dressing application of participants in group B that includes harvesting of donor skin, preparation and application of the ASCS to the wound followed by Biobrane® and secondary dressings. A suitable donor site, where possible, will be identified adjacent to the wound. The size of skin sample will be based on the TBSAB as determined by the RES™ preparation guidelines. A donor sample of healthy skin will be obtained at a depth of 0.15 mm (0.006 in.) in depth using a pneumatic dermatome (Zimmer, Dover, Ohio, USA). The correct thickness of donor is evidenced by an almost translucent sample that leaves behind pinpoint bleeding at the donor site, the edges of the sample do not curl and there is an absence of the white dermis surface. Any excess RES™ if present will be applied to the donor site then dressed with Cuticerin**®** (Smith and Nephew Medical Ltd., Hull, UK). The sequence of secondary dressings used in groups B and C will maintain moisture, allow for absorption of exudate and a degree of compression to minimise disturbance of the fragile epidermal surface. Application of these dressing changes is not required under general anaesthesia unless otherwise indicated. The attending burns surgeon or paediatric surgery registrar assigned to the care of the patient will apply the RES™ and Biobrane®. Both doctors and nurses will apply the standard silver dressings.

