### Scar severity

The re-epithelialised wound will be evaluated for the severity of scars using objective (ultrasonography and colorimetry) and subjective (POSAS and Brisbane Burn Scar Impact Profile (BBSIP)) measures [63–66]. The objective measures are the principal approach based on evidence of the ability to detect change. Scar thickness will be measured using the portable Venue40 MSK® Ultrasound machine (GE Healthcare, Fairfield, CT, USA). Ultrasound test-retest and interrater reproducibility of scar thickness is acceptable for paediatric scars [67].

Scar colorimetry will be evaluated with the DSM II ColorMeter® (Cortex Technology, Hadsund, Denmark). This device uses tristimulus reflectance, colorimetry and narrow-band photometry to assess scar lightness (L*), erythema (a*) and pigmentation (b*) [68]. An average of three measurements of L*, a*, b* from both the scar and healthy skin will be recorded. The primary measure of scar pigmentation and scar erythema will be L* and a* respectively.

Both the investigator and guardian of all participants will complete the POSAS. This survey assesses scar thickness, vascularity, pliability, pigmentation and relief, as well as patient scale items of itch, pain, colour, stiffness, thickness and irregularity [63]. The BBSIP physical scar subscales and BBSIP sensory subscale will also measure scar severity [64–66]. An investigator having completed scar assessment training to the satisfaction of the occupational therapist at the study site will complete the scar assessments of all participants.

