### Blinding

Once data collection is complete, a panel of burn wound specialists inclusive of preselected burn surgeons and nurses will conduct a blinded review of wound and scar imaging. Any possible identifying material that could indicate to the blinded assessors, which group the participant, was allocated to, will be removed from images. The participants and their care providers will be blinded to their intervention assignment. Although it will be unavoidable to detect remnants of silver dressing in some cases, it is anticipated that it will be almost impossible to differentiate between the group B and group C. An experienced radiographer from the study centre will complete blinded assessments of scar thickness.

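### Group B alone has a planned donor wound, beside the burn where possible, so the statement that B and C can hardly be told apart does not hold for anyone who sees the child

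*Protocol article*

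**What the plan says.** Operative procedures (text following Table 1) describes a harvest step for group B only. "A donor sample of healthy skin will be obtained at a depth of 0.15 mm (0.006 in".) with a pneumatic dermatome. On its extent: "The size of skin sample will be based on the TBSAB as determined by the RES™ preparation guidelines". On its location: "A suitable donor site, where possible, will be identified adjacent to the wound". On its treatment: "Any excess RES™ if present will be applied to the donor site", after which it receives a dressing of its own. Group C receives Biobrane without any harvest (Interventions).

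The Blinding section concedes that traces of silver may sometimes be visible, then continues: "it is anticipated that it will be almost impossible to differentiate between the group B and group C". The one masking step it describes is that anything that could reveal "which group the participant, was allocated to, will be removed from images" before a panel reviews them. It then adds: "An experienced radiographer from the study centre will complete blinded assessments of scar thickness".

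Scar severity makes the objective measures the principal approach. Thickness is measured with a portable ultrasound machine. Colour readings "from both the scar and healthy skin will be recorded". The same section assigns the scar assessments of all participants to a trained investigator and does not say whether that person is blinded. Scar severity is a secondary outcome; according to the Abstract, secondary outcomes are assessed at dressing changes and at 3, 6 and 12 months.

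**The concern.** Comparing B with C is the only way this design isolates what the cell suspension adds to Biobrane. The Blinding section makes a positive claim about exactly that pair of arms. Its only acknowledged clue, silver residue, bears on group A. It overlooks the one physical difference that the operative procedure itself creates between B and C, and which by preference lies next to the area to be assessed.

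Ultrasound thickness depends partly on the operator, who decides where the probe goes. An operator who knows or guesses the arm could, without intending to, choose a thicker or thinner part of the scar. If the trial report repeats the blinding claim as written, readers will give the B versus C thickness result more protection from assessor bias than the described procedures provide.

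**Working it through.** The protocol gives no figure for unblinding or for how long a donor site stays visible, so there is nothing to recompute. The check sets the sections side by side.

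1. **Who has a donor wound by design?** Under Interventions and Operative procedures, harvesting is part of the initial dressing application in group B. Groups A and C have no such step.

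2. **Where is it?** Beside the burn where possible. Adjacency is the stated preference, not a certainty, so some group B children will have a donor site elsewhere.

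3. **Does the masking cover it?** The described step removes identifying material from images. A photograph can be cropped or edited so that a donor area does not show. Nothing comparable is described for a person examining the child.

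4. **Does anyone assess thickness with the child in view?** Someone must hold the probe. There are two readings of the article:
   - The radiographer named under Blinding both scans and measures. The assessor called blinded then sees the skin around the scar, with no covering described.
   - The investigator named under Scar severity scans, and the radiographer measures stored sonograms. The radiographer may then be masked, but the person who chose the probe position has no stated masking.

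   On either reading, at least one step of the measurement is open to a visible donor mark.

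5. **How many children?** The Sample size estimate gives 84 participants in 3 groups: 84 / 3 = 28 per group. At most, 28 group B children could be affected at each of 3 long-term visits: 28 × 3 = 84 child-visits, before attrition. This is a ceiling. The true number depends on how many donor sites are adjacent and how many are still visible, and the article reports neither.

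6. **Conclusion of the comparison.** The statement that B and C are nearly indistinguishable can stand for suitably masked images. It cannot stand as a general statement alongside the harvesting procedure.

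**The case against.** The strongest reply is that the article never says the radiographer examines the child. Data collection and storage lists sonography with photographs under clinical imaging, and Scar severity gives the assessments to an investigator, so the radiographer may only read stored scans on which no neighbouring donor mark would appear. This stands against any claim that the radiographer is unblinded. It does not remove the point, because the person acquiring the scan would then have no stated masking.

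Second, visibility is assumed. The harvest is very thin, and nothing shows that its mark persists to 3, 6 or 12 months or could be distinguished from the edge of the burn. This also stands: the supportable wording is that an assessor may be able to tell, not that one can.

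Third, a donor mark need not be exclusive to group B. The primary outcome definition foresees skin grafting, so a grafted child in A or C could also carry one. That makes the mark an imperfect signal, but only in group B is it planned for every child.

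Fourth, a condensed article may leave scanning details to the full protocol. That would answer a complaint about missing detail. It does not answer a stated blinding property that another section contradicts.

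A reader might also infer that the donor area could serve as the colour reference and so bias colorimetry in favour of the cell suspension. The documents do not support this. The reference is specified as healthy skin, which on a natural reading excludes a harvested site. No scar-minus-skin difference is defined as the outcome, no blinding is claimed for colorimetry, and the direction of any error would depend on whether the donor area were redder or paler than normal skin.

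**Conclusion.** The point holds in a limited form. The Blinding section's statement about groups B and C is contradicted by the operative procedure for anyone who sees the child, because group B alone has a donor wound by design and masking is described for images only. Whoever acquires the thickness scan may therefore be able to recognise group B.

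The consequence is weaker protection against assessor bias in one secondary outcome, ultrasound scar thickness, for the B versus C contrast. The ceiling is 28 children per visit at three visits; neither the actual number nor any resulting bias can be estimated from the article. The conclusion assumes that at least some adjacent donor sites are still visible when scans are taken and that the surrounding skin is not covered. It does not show that the radiographer is in fact unblinded or that the colour results are biased, and it makes no claim about the primary outcome.

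**What to change.** - **Blinding section.** Acknowledge the group B donor site as a possible clue, and limit the claim about telling B from C to images that have been masked.
- **Who does what.** State who acquires the ultrasound scan and who measures thickness, so that Scar severity and Blinding agree.
- **Scanning at 3, 6 and 12 months.** Determine the scan site by a written rule that is the same in all arms, so that no one chooses it at the visit. Before scanning, cover the surrounding skin, including any donor site, with an opaque drape in every arm. Alternatively, have the blinded radiographer measure stored, de-identified sonograms; the fixed site rule is then still worth keeping, because the person scanning may not be masked.
- **Minor safeguard for colorimetry.** Take the healthy-skin reading away from any donor site, by the same rule in all arms. The rule must work for burns at any anatomical location, so it cannot rely only on a mirror-image site.

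None of this changes the harvesting procedure or any treatment. The cost is a drape, a few lines of text and about a minute more per visit, with no extra staff or visits.
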